
**Fig. 1 fig0001:**
[figure not shown]
Flow chart of the study.

### Blinding

A single-blind approach will be employed. Outcome assessors will remain blinded to group allocation to minimise bias in outcome ascertainment. Participants and therapists cannot be blinded due to the nature of the intervention. The success of assessor blinding will be assessed by asking the blinded outcome assessor to guess the participant’s group allocation as intervention, control or unsure after each assessment. Responses will be summarised descriptively and quantified using Bang’s Blinding Index [22].

### Intervention

Participants in the intervention group will receive a structured physiotherapy program in addition to their usual care. The sessions will be delivered by the main researcher (first author), a trained physiotherapist with >10 years of experience with children with ASD, using a standardised protocol to ensure consistency. Session checklists and corrective feedback logs will ensure fidelity.

Session Structure and Delivery: The structured physiotherapy programme will be delivered in small groups of 2 participants, with 2 60-minute sessions per week across 12 weeks (24 sessions). Each session follows a standardised structure: 5–8 min of warm-up, 40–45 min of core activities, and 5–7 min of cool-down and sensory regulation. Guided by the FITT (Frequency, Intensity, Time, Type) principle, the intervention integrates coordination, balance, strength, aerobic endurance and flexibility training progressively. Table 1 summarises the structured physiotherapy intervention. Neuromotor skills are addressed through bilateral integration and sequencing tasks; balance through static and dynamic challenges such as obstacle courses and beam walking; strength via age-appropriate resistance training (1–3 sets of 8–12 repetitions), aerobic endurance through game-based moderate-intensity activities and flexibility through dynamic stretches and yoga-inspired movements. The programme is delivered in three progressive phases: preparatory (weeks 1–4), development (weeks 5–8), and consolidation (weeks 9–12). Frequency involves two sessions per week. Intensity will progress from low to moderate (50–60 % HRmax) in the preparatory phase and gradually increase to moderate to vigorous (60–70 % HRmax) in the development and consolidation phases, depending on each child’s baseline motor abilities and tolerance. The whole sequence of activities is detailed in Table 1. Parents will be encouraged to participate in the sessions by observing and engaging with selected activities alongside their child. The parents’ involvement aims to reinforce motor learning, strengthen parent–child interaction, and facilitate continuity of practice through daily home activities.

**Table 1 tbl0001:** Summary of structured physiotherapy intervention.

Phase	Objectives	Components
Week 1–4 Preparatory Phase	Familiarisation with the strength, coordination, endurance and flexibility components in the training. Explore body segments; improve upper limb and lower limb coordination; low intensity training; breathing control	Warm-up: Mobility & breathingEndurance: Trampoline jumping, Figure-8 walkingStrength: Gymball lifts, Dumbbell raises, Wall squatsCoordination: Bear crawl, Arm circleBalance: Tandem walk, Tree pose
Week 5–8 Development Phase	Build strength, coordination and endurance. Develop unilateral strength, balance & symmetry; moderate intensity; breathing control	Warm-up: Light aerobicEndurance: Run + bean bag scrambleStrength: Medicine ball slams, Biceps curl, Frog jumpsCoordination: Catch/throw beanbagBalance: Beam walk
Week 9–12 Consolidation Phase	Develop strength, coordination, endurance and flexibility; focus on social-interaction task activity; high-intensity control; breathing control	Warm-up: TrampolineEndurance: Running + hurdlesStrength: Towel pull, BridgingCoordination: DribblingBalance: Single-leg variations

Assessment and Monitoring: Children’s heart rate will be monitored using a standard finger pulse oximeter, which provides real-time heart rate readings in addition to oxygen saturation. Age-predicted HRmax calculated using the formula: 220 – age [23]. Measurements will be taken at least twice during the aerobic component of each session, once at mid-point and once near the end, to ensure that activities remain within the targeted intensity range. In cases where children do not tolerate the pulse oximeter, intensity will be monitored using the OMNI Paediatric Perceived Exertion Scale and by observing behavioural indicators, such as breathing rate and speech ability. The measure will be recorded at each session to cross-validate intensity. Task progression is determined using a standardised 4-point technique checklist (1 = unable, 2 = requires assistance, 3 = independent with errors, 4 = independent with correct technique). The 4-point technique assessment is conducted by the treating physiotherapist during task performance and recorded on standardised forms for progression decisions. Progression occurs when the child achieves level 3–4 performance on ≥75 % of task attempts within a session. Progression made based on the guidelines provided by the American College of Sports Medicine 2020 [24]. Correct technique will be defined as the ability to perform ≥75 % of task repetitions with the intended movement pattern, posture and range of motion as demonstrated during training by the physiotherapist. If a child is unable to achieve this threshold, the activity will be regressed to a simpler form. For strengthening exercise, children will complete 1–3 sets of 8–12 repetitions, with resistance increased via bands or added complexity once children perform ≥75 % of tasks with correct technique. Aerobic activities will gradually increase from 8 to 15 min per session. Balance and coordination challenges will advance by reducing external support, increasing speed, or adding dual-task elements. Short breaks are provided between tasks to accommodate individual needs. If a child refuses to perform an activity, the session proceeds to the next task, and all completed activities are recorded.

Group Management Strategy: Within each 4-week phase, the same core activities are maintained to allow skill consolidation, but their complexity is progressively increased based on individual performance. Progression occurs when a child demonstrates ≥75 % correct technique, regardless of the week within the phase. One example is during the preparatory phase (weeks 1–4), all children practice the same core balance activity (single-leg stance). However, progression occurs individually: starting with eyes open/arms free, advancing to eyes closed, then adding dual tasks, regardless of which week within the phase. New activity types are only introduced in subsequent phases. Each child’s progression will be individualised based on their ability to perform tasks with correct technique and tolerance. If one child progresses more rapidly than another, the physiotherapist will adjust the session by maintaining the same activity theme while assigning tasks at different levels of difficulty. These adjustments may involve modifying parameters such as distance, load, or balance demands (e.g., shorter versus longer distances, lighter versus heavier balls, or wider versus narrower balance paths). For instance, when implementing the balance beam activity for individualised progression and regression in a group setting, different strategies can be applied based on each child's skill level. For children who have not achieved at least 75 % correct technique, regression strategies include widening the beam, reducing walking speed, and simplifying the task to forward walking only. Conversely, for those who meet the progression threshold, the task can be advanced by narrowing the beam width, increasing walking speed, and introducing a dual-task element, such as carrying an object while walking across the beam. This approach helps maintain group cohesion while providing an appropriate level of challenge for each child. Activities will be delivered in pairs, allowing for social interaction while accommodating differences in ability [25]. This paired approach ensures that children benefit from the motivational and social aspects of group participation while receiving individualised progression appropriate to their developmental level [25]. The physiotherapist will supervise both children simultaneously, ensuring safety, engagement, and consistency of delivery.

### Control group

Participants in the control group will continue with usual care only, defined as the range of therapeutic services accessible through routine clinical pathways at the participating centres. These typically include occupational therapy focusing on sensory integration and fine motor activities, speech-language therapy addressing social communication and pragmatic language goals, and clinical psychology sessions targeting behavioural regulation. In routine clinical practice, the frequency of these services varies according to service availability and individual care plans. Occupational therapy is commonly delivered on a monthly basis, while speech-language therapy and clinical psychology are typically provided at longer intervals, often approximately once every six months. The specific content and frequency of usual care may therefore vary across participants and centres, reflecting the heterogeneity of routine clinical practice. The frequency and intensity of these therapies will be recorded using standardised caregiver logs and verified with site records. During the 12-week study period, no additional structured motor-based intervention will be introduced. To minimise contamination, participants will be asked not to enrol in new motor-based programmes, and site clinicians will be informed of this restriction. A usual-care control group was selected to reflect real-world practice and enhance the external validity of the trial findings.

### Outcome measures

The primary outcome of this study is motor skill level. Motor skills will be measured using the BOT-2 Short Form, which is widely recognised as a comprehensive and standardised tool for assessing both fine and gross motor skills in children [26]. BOT-2 Short Form measures 4 motor area composites with 8 subtests comprised of 14 items. The BOT-2 Short Form includes subtests covering manual coordination, body coordination, strength, and agility. Standard scores will be calculated using age-specific norms, with higher scores indicating better motor performance. The BOT-2 has demonstrated strong reliability and validity in populations with ASD [27].

Secondary outcomes include autism symptoms, physical activity levels, behavioural problems, and QoL. Physical activity levels will be measured using the Godin–Shephard Leisure-Time Exercise Questionnaire (GLTEQ), a validated self-report tool adapted for proxy reporting by parents in paediatric populations [28]. The GLTEQ assesses the frequency of mild, moderate, and vigorous leisure-time physical activity over a typical 7-day period. The questionnaire comprises four items, requires approximately 10–15 min to complete, and yields categorical classifications: ≥24 units = Active; 14–23 units = Moderately Active; < 14 units = Insufficiently Active/Sedentary. A total leisure activity score is derived by weighting responses according to intensity, with higher scores indicating greater engagement in physical activity. Previous studies have confirmed GLTEQ’s validity and reproducibility in monitoring physical activity among children with ASD [29].

Autism symptoms and severity will be assessed using the GARS-3, a validated tool for assessing autism-related behaviours in children [30]. The scale includes 58 items across six subscales: Restricted/Repetitive Behaviours, Social Interaction, Social Communication, Emotional Responses, Cognitive Style and Maladaptive Speech [30]. Items are rated on a 4-point frequency scale to generate subscale scores and an overall autism index, with higher scores indicating greater severity [30]. The GARS-3 demonstrates strong psychometric properties and is widely used in both clinical and research settings [30].

Behavioural problems will be evaluated using the Child Behaviour Checklist (CBCL), a parent-reported questionnaire designed to evaluate emotional and behavioural functioning in children [31]. The CBCL includes 118 items, with responses rated on a 3-point scale (“Not True”, “Somewhat or Sometimes True”, “Very True or Often True”) [31]. Composite scores will be generated for internalising problems, externalising problems, and total behaviour problems. The CBCL has been widely validated internationally, including in ASD populations, and provides a robust measure of behaviour-related changes following intervention [32].

Quality of life will be assessed using the Paediatric Quality of Life Inventory (PedsQL), which measures health-related quality of life across four domains: physical, emotional, social, and school functioning [33]. The 23-item parent-proxy form will be administered, with responses rated on a 5-point Likert scale from “Never” to “Almost Always”. Items are reverse-scored and linearly transformed to a 0–100 scale, with higher scores reflecting better QoL [33]. The PedsQL has strong psychometric properties and has been validated for the ASD population [34].

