## Background

Autism Spectrum Disorder (ASD) affects approximately 1 in 36 children globally and represents a growing public health concern [1]. ASD is characterised by persistent difficulties in social communication and restricted, repetitive behaviours [2]. Beyond these core diagnostic characteristics, children with ASD commonly demonstrate motor impairments, including poor coordination, impaired balance, and delayed fine and gross motor skill development [3]. Evidence indicates that 80–88 % of children with ASD present motor impairments of clinical significance [4,5]. These motor impairments interfere with age-appropriate physical play, school-related movement tasks, and sport participation, which may reduce independence, limit peer interaction, and contribute to poorer overall quality of life (QoL) [6,7].

Neurobiological evidence supports the need for targeted motor rehabilitation [8]. Motor impairments in ASD are associated with altered cerebellar–cortical connectivity, contributing to deficits in balance control and motor planning [8]. Neuroimaging studies demonstrate reduced cerebellar volume and disrupted signalling between the cerebellum and the primary motor cortex, impairing implicit motor learning, a process typically acquired automatically through play in typically developing children [9]. Consequently, children with ASD more consistently benefit from structured programmes involving high repetition and explicit feedback, rather than unstructured motor practice alone [10].

A wide range of motor and exercise-based interventions has been evaluated in children with ASD, including fundamental motor skill programmes, yoga, rhythmic movement, aquatic therapy, exergaming, physical education, and general physical activity initiatives [[11], [12], [13]]. While these interventions show promising results, the evidence remains heterogeneous, with substantial variability in duration, frequency, supervision, instructor expertise, and progression criteria, limiting comparability and clarity about optimal treatment parameters [[11], [12], [13]]. Many programmes examine motor outcomes in isolation without evaluating broader functional pathways or QoL [14,15]. This leaves limited clarity about whether motor improvements translate into physical activity participation, behavioural gains, or QoL changes [[13], [14], [15]].

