### Participant screening, recruitment and randomisation

All children with ASD will be screened and recruited from the sampling frame of participating centres, using simple random sampling. The screening, recruitment, and randomisation procedures will be conducted by an independent researcher who is not involved in data collection or outcome assessment. Screening assessments of GARS-3 and BOT-2 Short Form will be conducted before randomisation to determine eligibility. As these assessments will be administered immediately before group allocation and under the same standardised conditions required for baseline measurement, the screening scores will be used as baseline data to minimise participant burden and avoid unnecessary repetition of measures. Eligible participants and their caregivers will receive clear, comprehensive information about the study through written materials and verbal explanations. This will include the study objectives, procedures, potential risks and benefits, and the anticipated time required for participation. After confirming their understanding, parents or legal guardians will be asked to provide written informed consent. Assent will also be obtained from the participating children in accordance with ethical standards for research involving minors. Only children classified as having mild to moderate ASD according to the GARS-3 will be invited to attend a motor skills assessment using BOT-2 Short Form. If a selected participant declines, the next name on the list will be contacted to achieve the desired recruitment target. Screening will take place over a two-week period, during which eligibility will be confirmed. Following confirmation of eligibility, participants will be randomised into either the intervention or control group using a computer-generated randomisation sequence (randomization.com). To reduce potential confounding, stratified randomisation will be applied by age group (6–8 years vs. 9–10 years) and ASD severity (mild vs. moderate, based on GARS-3). This approach will balance participant characteristics across study arms and ensure that outcomes reflect the intervention's effect independent of these variables. Allocation concealment will be maintained to prevent selection bias. Children who are successfully randomised will then be scheduled for baseline parent proxy assessments, conducted before the initiation of the intervention. GARS-3 and BOT-2 Short Form scores obtained during screening will serve as baseline values, while the GLTEQ, CBCL, and PedsQL will be administered as parent-proxy assessments following randomisation but before the intervention begins. All five outcome measures will be re-administered at post-intervention. This sequence ensures that group allocation is unbiased and that baseline data reflect participants’ pre-intervention status. A SPIRIT schedule of enrolment, interventions, and assessments is shown in Fig. 1.

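### The GLTEQ definition leaves open whether the trial's own sessions count, and only one arm has them, so a group × time effect may partly reflect attendance

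*Protocol article*

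**What the plan says.** The Outcome measures section lists physical activity level as a secondary outcome, measured by the GLTEQ, which it describes as "a validated self-report tool adapted for proxy reporting by parents in paediatric populations". The construct and window are given as: "The GLTEQ assesses the frequency of mild, moderate, and vigorous leisure-time physical activity over a typical 7-day period". On scoring: "A total leisure activity score is derived by weighting responses according to intensity, with higher scores indicating greater engagement in physical activity". The categories are "≥24 units = Active; 14–23 units = Moderately Active; < 14 units = Insufficiently Active/Sedentary". Numeric weights are not given.

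The Intervention section gives the intervention arm "2 60-minute sessions per week across 12 weeks (24 sessions". Intensity is to "gradually increase to moderate to vigorous (60–70 % HRmax) in the development and consolidation phases". The aerobic part is game-based, children work in pairs, and parents are encouraged to join in.

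The Control group section adds no structured motor programme for controls and asks participants not to take up new ones.

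Under Participant screening, recruitment and randomisation, the baseline GLTEQ is completed after randomisation but before the intervention starts. For follow-up the text says: "All five outcome measures will be re-administered at post-intervention". It names no rated week and no interval after the last session. Data analysis specifies a 2 × 2 group × time mixed ANOVA.

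**The concern.** The score is a weekly frequency count weighted by intensity. The trial supplies two weekly occasions of exercise to one arm and none to the other. Unless parents leave those occasions out, the outcome partly records receipt of the intervention.

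The imbalance falls on the effect being tested. No baseline form can contain a trial session, and no control form can contain one at either time. A counted session can enter only the intervention arm's post-intervention score. An apparent gain in physical activity could then be reported although the child does nothing more outside the programme than before.

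Parents may also decide differently from one another, since nothing in the article settles the matter. That would add noise as well as bias. The limitations section warns that parent-reported GLTEQ data may be affected by subjective perception and social desirability, but does not mention this overlap.

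**Working it through.** The article states no figure for this overlap, so there is none to reproduce. The check asks how large it could be.

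**Inputs from the article:** 2 sessions per week, intervention arm only; category bounds at 14 and 24 units; 32 children per arm; significance level 0.05.

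**Assumptions, not in the article:** weights of 3, 5 and 9 units per mild, moderate and vigorous occasion; each session counted once; full attendance; no displacement of other activity; SD of the change score of 10, 20 or 25 units.

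**Step 1. The effect tested.** With two time points, the group × time interaction is

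(intervention post − intervention baseline) − (control post − control baseline).

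If activity outside the sessions does not change in either arm, and a share p of sessions is counted, this equals 2wp. It is zero only if p = 0.

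**Step 2. Size with every session counted (p = 1).** The middle band runs from 14 up to the next bound at 24, so its width is 24 − 14 = 10 units.

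| Assumed w | Added units, 2w | Other activity needed to reach 14 (14 − 2w) | Other activity needed to reach 24 (24 − 2w) |
|---|---|---|---|
| 3 | 6 | 8 | 18 |
| 5 | 10 | 4 | 14 |
| 9 | 18 | none (18 already exceeds 14) | 6 |

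Without assuming particular weights, any w of 5 or more adds at least a full band width. Any w of 7 or more puts a child with no other activity at 14 or above.

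**Step 3. Chance that attendance alone gives a significant result.** The interaction test is a comparison of mean change between arms. With Δ = 2w and n = 32 per arm, the approximate chance is Φ(Δ / (SD × √(2/n)) − 1.96), where √(2/32) = 0.25. For example, Δ = 10 and SD = 20 give 10 / (20 × 0.25) = 2.00, and Φ(2.00 − 1.96) = 0.52.

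| Assumed SD of change | w = 3 | w = 5 | w = 9 |
|---|---|---|---|
| 10 | 0.67 | 0.98 | 1.00 |
| 20 | 0.22 | 0.52 | 0.95 |
| 25 | 0.16 | 0.36 | 0.82 |

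The smallest entry, 0.16, is about three times the nominal 0.05.

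**Step 4. Partial counting.** If half of the sessions are counted (p = 0.5), the shift is 3, 5 or 9 units. At SD 20 the chance becomes Φ(0.60 − 1.96) = 0.09, Φ(1.00 − 1.96) = 0.17 and Φ(1.80 − 1.96) = 0.44. The direction needs only a positive weight and some counting. The size depends on the assumptions.

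**The case against.** **The text says leisure-time activity.** A reader might infer that the GLTEQ counts all exercise. The article does not say so, and a parent may well regard therapist-led physiotherapy as something other than leisure. This limits the certainty of the bias but does not remove it: the sessions are game-based, done in pairs and open to parents, and the article gives no rule.

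**The rated week is not fixed.** A reader might infer that parents describe a week within the programme. The article says only that measures are repeated post-intervention. If the rated week falls after the sessions end, the overlap may be small or absent. This stands, and it is why the point is that the score can be inflated, not that it will be.

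**Total activity may be the target.** The Background says of earlier work: "This leaves limited clarity about whether motor improvements translate into physical activity participation". A reader might take carry-over as this trial's stated question. That sentence criticises previous studies. The abstract speaks simply of physical activity levels, and no carry-over analysis is described. If total activity is wanted, programme sessions are real activity and belong in it. This stands, and is met by reporting both totals.

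**The article is condensed.** The full protocol or the form may carry an instruction that is not shown. That is possible. However, the article goes as far as giving the construct, window, scoring principle and cut-points, and following that definition as stated permits the overlap.

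**Home practice.** The intervention also encourages daily home activities, which excluding trial sessions does not touch. This stands as a residual limit on interpretation.

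**Conclusion.** The concern holds as a weakness in the definition of one secondary outcome. The article neither excludes trial sessions from the GLTEQ nor fixes the rated week, and any counted session inflates the post-intervention score in the intervention arm alone. A significant group × time effect on this outcome could not then be separated from attendance.

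The shift is 2w units under full counting: 6, 10 or 18 for assumed weights of 3, 5 and 9. It is proportionately less if only some sessions are counted. The probabilities of a significant result rest in addition on assumed SDs and illustrate scale only.

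A reader might infer that 10 units carry a child from Insufficiently Active to Active. On the article's cut-points they do not: the highest whole-number score in the lowest band is 13, and 13 + 10 = 23 is still Moderately Active. Ten units is the width of the middle band. Only at the assumed weight of 9 would such a jump occur, for children with 6 to 13 units of other activity.

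Nothing here bears on the BOT-2 primary outcome or the sample size.

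**What to change.** At post-intervention, instruct parents in both arms to report leisure-time activity excluding the trial's physiotherapy sessions, and state the reference week. Make this total the GLTEQ outcome. Add a separate line recording trial sessions, so that the total including them can also be reported and a reader interested in overall activity is served.

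Limit the exclusion to trial sessions. The Protocol validation section says recruitment and delivery are under way. Although it also says outcome assessments have not commenced, some baseline GLTEQ forms may already be complete, because they precede the intervention. Those forms cannot contain trial sessions and so stay comparable. Excluding other scheduled therapy as well would change the construct between baseline and follow-up for those children.

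The cost is one instruction and one item added to a validated form, with no extra visits or staff.
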